### Blinding

Due to the interventional trial design, participants and instructors (i.e. strength training and ergonomics instructors) could not be blinded to group allocation. However, outcome assessors and data analysts were blinded to group allocation.

### Outcome measures

Outcomes were measured by trained clinical examiners and by questionnaire survey at baseline and after the 10 week intervention period.

#### Primary outcome measures

The primary outcome is the change from baseline to 10-week follow-up in pain intensity during the last week (average of 3 regions; shoulder, elbow/forearm and hand/wrist, respectively). Pain intensity was rated subjectively using a 0–10 modified VAS scale, where 0 indicates “no pain at all” and 10 indicate “worst pain imaginable” [36,40]. The shoulder, elbow/forearm and hand/wrist regions were defined by drawings from the Nordic questionnaire [41].

#### Secondary outcome measures

The work module of the Disability of the Arm, Shoulder and Hand questionnaire (DASH) was recorded and analyzed in the same way as the primary outcome. The participants replied to the following questions: “Select which best describes your physical ability in the past week. Did you have any difficulty.....1) Using your usual technique for your work? 2) Doing your usual work because of arm, shoulder or hand pain? 3) Doing your work as well as you would like? 4) Spending you usual amount of time doing your work?”. The possible answers to each question are: “No difficulty, Mild difficulty, Moderate difficulty, Severe difficulty, Unable” [19].

A physiotherapist performed a thorough clinical examination of the shoulder, arm and hand of all participants at baseline and follow-up physical examination, respectively. Examiner-verified palpable tenderness (scale ‘none’, ‘light’, ‘moderate’ and ‘severe’) of the muscles in the shoulder, arm and hand were summed up to a total tenderness score [36,42]. The change in the total tenderness score from baseline to week 10 was calculated.

Maximal muscle strength and function of the arm and hand was assessed by maximal isometric voluntary contractions in a custom-built dynamometer setting. The strength tests were part of the physical examination at baseline and follow-up.

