**Methods/design:**

66 slaughterhouse workers were allocated to 10 weeks of (1) strength training of the shoulder, arm and hand muscles for 3 x 10 minutes per week, or (2) participatory ergonomics involving counseling on workstation adjustment and optimal use of work tools (~usual care control group). Inclusion criteria were (1) working at a slaughterhouse for at least 30 hours per week, (2) pain intensity in the shoulder, elbow/forearm, or hand/wrist of at least 3 on a 0–10 VAS scale during the last three months, (3) pain lasting for more than 3 months, (4) frequent pain (at least 3 days per week) (5) at least moderate work disability, (6) no strength training during the last year, (7) no ergonomics instruction during the last year.

Perceived pain intensity (VAS scale 0–10) of the shoulder, elbow/forearm and hand/wrist (primary outcome) and Disability of the Arm, Shoulder and Hand (Work module, DASH questionnaire) were measured at baseline and 10-week follow-up. Further, total muscle tenderness score and muscle function were assessed during clinical examination at baseline and follow-up.

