### Statistical analysis

All statistical analyses will be performed using the SAS statistical software for Windows (SAS Institute, Cary, NC). The change in pain (0–10 scale) will be evaluated using a repeated-measures two-way analysis of variance (ANOVA) with *group*, *time* and *group by time* as independent variables. Subject is entered as a random effect. Analyses are adjusted for gender, workplace, age and pain intensity at baseline. We will perform all statistical analyses in accordance with the intention-to-treat principle using a Mixed model approach which inherently accounts for missing values. An alpha level of 0.05 will be accepted as significant. Outcomes will be reported as between-group least square mean differences and 95% confidence intervals from baseline to follow-up.

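### The repeated-measures model applied to the DASH work module (and to pain) yields a change-score contrast, which is less precise than analysis of covariance on each outcome's own baseline

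*Protocol article*

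**What the plan says.** Under Secondary outcome measures, the protocol article states that the DASH work module "was recorded and analyzed in the same way as the primary outcome". The Statistical analysis section gives one model, worded for pain: a repeated-measures two-way ANOVA with group, time and their interaction. It adds "Subject is entered as a random effect" and "Analyses are adjusted for gender, workplace, age and pain intensity at baseline". The result to be reported is described as follows: "Outcomes will be reported as between-group least square mean differences and 95% confidence intervals from baseline to follow-up".

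Outcome measures fixes two measurement times, "at baseline and after the 10 week intervention period". The Abstract confirms that both pain and DASH "were measured at baseline and 10-week follow-up", so baseline DASH is in hand. For the tenderness score the article says only "The change in the total tenderness score from baseline to week 10 was calculated"; that defines a variable and names no between-group model. Baseline DASH is nowhere named as a covariate.

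**The concern.** Work disability is in the trial's title and aim, and DASH is the first secondary outcome listed. A model with group by time over two occasions treats the baseline value as a response and does not condition on it. The treatment contrast is then a comparison of raw changes. This has two costs. The interval is wider than the data require. A chance difference between the arms in baseline DASH also passes into the estimate, although the value that would remove it has been collected. With 33 per arm, chance differences are to be expected: Table 2 already marks age (43 versus 48 years) as differing between groups, and it shows no baseline DASH.

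**Working it through.** **1. The plan's own figure.** The article gives no design figure for DASH. Its pain calculation reproduces. With difference 1.5, SD 1.5, two-sided alpha 0.05 and 95% power, the normal formula gives 2 × (1.96 + 1.645)² × (1.5/1.5)² = 26 per group. The noncentral t gives power of 94.2% at 26 and 95.0% at 27. Then 27/0.9 = 30. The sample size is not at issue.

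**2. What the contrast estimates.** With two occasions, the group-by-time coefficient is (week 10 minus baseline, strength training) minus (week 10 minus baseline, ergonomics). A covariate entered as a subject-level main effect adds the same amount at both occasions and cancels from each difference. In complete data the estimate is therefore the raw difference in mean change, whether the covariate is baseline pain, baseline DASH or neither.

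**3. Precision.** Take equal variances s² at both times and correlation rho. The change score has variance 2(1 − rho)s². The residual variance after adjustment for own baseline is (1 − rho²)s². The ratio of the second to the first is (1 + rho)/2, so the change-score interval is wider by the factor √(2/(1 + rho)). The article gives no rho; a range is assumed.

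| rho | variance ratio | change-score interval relative to ANCOVA | ANCOVA interval narrower by |
|---|---|---|---|
| 0.3 | 0.65 | 1.240 | 19% |
| 0.5 | 0.75 | 1.155 | 13% |
| 0.7 | 0.85 | 1.085 | 8% |
| 0.8 | 0.90 | 1.054 | 5% |

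At rho 0.5 the gain is worth 1/0.75 = 1.33, that is, one third more participants.

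**4. Chance imbalance.** If the arms differ by d in mean baseline DASH, the change-score estimate is shifted by (1 − rho)d in size. With 33 per arm the standard deviation of d is √(2/33) = 0.246 s. An imbalance of that size shifts the estimate by 0.17 s, 0.12 s or 0.07 s at rho 0.3, 0.5 or 0.7.

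**5. Simulation of the stated model.** Settings: 33 per arm, two occasions, random intercept, REML, complete data, no true effect, 2,000 runs per rho, one baseline covariate at a time, assumed baseline pain–DASH correlation 0.5, outcomes in SD units. In every repeated-measures fit the estimate equalled the raw change difference (maximum deviation 0.0000).

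| rho | true SD of estimate | mean SE (rejection rate), baseline pain as covariate | mean SE (rejection rate), baseline DASH as covariate | mean SE, week-10 ANCOVA |
|---|---|---|---|---|
| 0.3 | 0.291 | 0.289 (5.2%) | 0.263 (7.2%) | 0.235 |
| 0.5 | 0.244 | 0.246 (4.7%) | 0.230 (6.6%) | 0.214 |
| 0.7 | 0.193 | 0.190 (5.3%) | 0.182 (6.3%) | 0.176 |

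Monte Carlo error on a 5% rejection rate is √(0.05 × 0.95/2000) = 0.5 percentage points.

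**6. Why the swap understates the standard error.** With baseline DASH as both response and covariate, its fitted slope is (1 + rho)/2. The residuals at the two times are then negatively correlated, and the random-intercept variance goes to zero. The pooled residual variance becomes [(1 − rho)²/2 + (1 − rho²)]/2. At rho 0.5 this is (0.125 + 0.75)/2 = 0.4375, where 0.5 is needed. The reported standard error is √(0.4375 × 4/33) = 0.230 against a correct √(0.5 × 4/33) = 0.246, as simulated.

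**The case against.** The article does not settle which baseline DASH is adjusted for. The model is written for pain, and pain is adjusted for its own baseline, so analysing DASH in the same way may well mean baseline DASH. A reader might infer that the plan rules out adjustment for baseline DASH; the text does not support that. Nor does the choice of covariate cause the loss. Steps 2 and 5 show that baseline DASH as a main effect leaves the estimate exactly where it was. This part of the objection stands, and it moves the problem from the covariate list to the response structure, where it touches pain as well.

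The cancellation in step 2 is exact only with complete data. The article expects 10% dropout and relies on the mixed model for missing values. In a small simulation with 10% of follow-ups missing, adding baseline pain moved the estimate by up to 0.09 SD. The change-score description is then approximate, though still close.

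The article also gives no DASH standard deviation, correlation or target difference, so no statement about power for DASH can be made. Covariates for secondary outcomes are often left to an analysis plan, which is not shown here. But the article does state a model and assigns DASH to it, so the structure is fixed in the text.

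**Conclusion.** The point holds as a matter of efficiency, for DASH and for pain alike. As written, the DASH contrast is in effect a raw change-score comparison, with an interval about 24%, 15.5% or 8.5% wider than analysis of covariance on baseline DASH at rho 0.3, 0.5 or 0.7. It is also exposed to chance baseline imbalance. The size rests on the assumed rho, equal variances at the two times and complete data.

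A reader might go further and call the DASH result biased, invalid or wholly unadjusted. The article does not support that. Under randomisation the change-score contrast is unbiased, and with baseline pain as covariate its test kept close to the 5% level in the simulation. Four covariates are listed, even if as main effects they do not move this contrast. The article also does not single DASH out as a main or key secondary outcome. The risk to test validity arises only if an outcome's own baseline is entered as a covariate while also kept as a response. That is one possible reading for DASH. It is also the literal reading for pain, so the model sentence itself needs correcting.

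**What to change.** In the Statistical analysis section, replace the model description with one of two options and let the DASH sentence under Secondary outcome measures refer to it:

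- **Analysis of covariance:** each outcome's week-10 value on group, gender, workplace, age and that outcome's own baseline value.
- **Constrained longitudinal model:** both occasions as responses with a common baseline mean in the two groups, adjusted for gender, workplace and age, and without the outcome's baseline as an additional covariate. This keeps participants with missing follow-up and so suits the stated intention-to-treat approach.

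Apply the choice to pain and DASH alike, and to tenderness and muscle strength if they are compared between groups. Do not simply put baseline DASH in place of baseline pain in the existing repeated-measures model. The cost is a rewritten model description, settled before the analysis; no new data, visits or participants are needed.

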### Sample size

A priori power analysis based on previous measurements revealed that 27 participants of each group for 95% power, SD of 1.5 and a minimal relevant difference of pain intensity of 1.5 [43] was sufficient to test the null-hypothesis of equality (α = 0.05). At an estimated 10% drop-out during the intervention period, group sizes were calculated to be at least 30.

### Statistical analysis

All statistical analyses will be performed using the SAS statistical software for Windows (SAS Institute, Cary, NC). The change in pain (0–10 scale) will be evaluated using a repeated-measures two-way analysis of variance (ANOVA) with *group*, *time* and *group by time* as independent variables. Subject is entered as a random effect. Analyses are adjusted for gender, workplace, age and pain intensity at baseline. We will perform all statistical analyses in accordance with the intention-to-treat principle using a Mixed model approach which inherently accounts for missing values. An alpha level of 0.05 will be accepted as significant. Outcomes will be reported as between-group least square mean differences and 95% confidence intervals from baseline to follow-up.

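### The primary model uses baseline pain as both the time-0 response and a covariate; with a zero-bounded random intercept this usually understates the group-by-time standard error, giving a type I error of about 5% to 9%

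*Protocol article*

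**What the plan says.** The Statistical analysis section of the protocol article gives one model for the primary outcome: a "repeated-measures two-way analysis of variance (ANOVA) with *group*, *time* and *group by time* as independent variables". It adds "Subject is entered as a random effect" and "Analyses are adjusted for gender, workplace, age and pain intensity at baseline". Results are to be given as "between-group least square mean differences and 95% confidence intervals from baseline to follow-up", so the contrast of interest is the difference in change, which is the group-by-time term. The test level is fixed: "An alpha level of 0.05 will be accepted as significant".

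The Outcome measures section gives two measurement times only: "at baseline and after the 10 week intervention period". The primary outcome is the change over that interval in last-week pain, averaged over three regions. Under Secondary outcome measures, the DASH work module is to be analysed like the primary outcome.

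**The concern.** A change score gives one record per worker, and with one record neither a time factor nor a random subject effect can be fitted. As written, the response must therefore be pain at both times, and baseline pain is one of the two responses. The adjustment sentence then puts the same value on the right-hand side, so the time-0 response is regressed partly on itself.

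The validity of the primary p-value and 95% confidence interval is at stake, because the model's residual variance no longer reflects how variable a worker's change in pain is. The adjustment also does not deliver the precision that a reader would expect from it.

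**Working it through.** **Inputs.** From the protocol article: 33 workers per group (Table 2), alpha 0.05, two measurement times, 10% drop-out (Sample size). Not in the document, hence assumed: the baseline–follow-up correlation r and the ratio k of follow-up SD to baseline SD for the three-region mean. Table 2 gives SDs for single regions at baseline only.

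**The plan's own figure.** With SD 1.5, difference 1.5 and two-sided alpha 0.05, power from the noncentral t is 0.942 at 26 per group and 0.950 at 27, and 27/0.9 = 30. The stated sample size reproduces and is not affected by this point.

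**Step 1: implied subject variance (k = 1, common SD s).**
- Within workers, the change has variance 2(1−r)s². The within mean square is half of that, (1−r)s², and estimates the residual variance.
- Between workers, the mean of the two values, given baseline, has variance (1−r²)s²/4. The between mean square is twice that, (1−r²)s²/2, and estimates residual variance + 2 × subject variance.
- Subject variance = [(1−r²)/2 − (1−r)]s²/2 = −(1−r)²s²/4, negative for every r below 1. For general k, with baseline SD 1, it is −(1−rk)²/4.

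**Step 2: what a zero bound does.** With the subject variance at 0, the residual variance pools both strata, which have nearly equal degrees of freedom (66 − 2 = 64 within, 66 − 6 = 60 between). It becomes about [(1−r²)/2 + (1−r)]s²/2 = (1−r)(3+r)s²/4. The correct value for group-by-time is (1−r)s², so model variance / true variance = (3+r)/4.

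A check at r = 0.5: the pooled slope on baseline is (1+r)/2 = 0.75. Baseline residuals have variance (1−0.75)²s² = 0.0625s², and follow-up residuals (1−0.25)s² + 0.0625s² = 0.8125s². Their average is 0.4375s², against the correct 0.5s²: ratio 0.875 = (3+0.5)/4. The small baseline residuals pull the variance down. Workers who drop out contribute only a baseline record, which pulls it further.

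**Step 3: type I error, equal SDs.** The closed form is 2[1−Φ(1.96 × SE ratio)]. The simulation used 3,000 null trials per setting, 33 per arm, REML with subject variance bounded at zero and all the listed covariates.

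| r | Variance ratio | SE ratio | Closed form | Simulated, complete | Simulated, 10% missing | Subject variance at 0 (complete) |
|---|---|---|---|---|---|---|
| 0.3 | 0.825 | 0.908 | 7.5% | 7.0% | 8.5% | 100% |
| 0.5 | 0.875 | 0.935 | 6.7% | 7.0% | 7.9% | 99.8% |
| 0.7 | 0.925 | 0.962 | 5.9% | 5.8% | 8.1% | 96.4% |

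The Monte Carlo standard error is about 0.5 points (√(0.07 × 0.93/3000) = 0.0047). Repeat simulations over the same r gave 5.4% to 7.4% with complete data and 6.2% to 8.7% with 10% drop-out. A smaller run (1,500 trials per setting, r from 0.3 to 0.8, complete data) gave 5.9% to 8.1%. At r = 0.5 with 10% missing, the mean model SE was 0.231 against a true SD of 0.262, a ratio of 0.88.

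**Step 4: unequal SDs (closed form, complete data, r from 0.3 to 0.9).** k = 0.8 gives 7.6% to 8.9%; k = 1.2 gives 5.0% to 6.6%. The effect vanishes as the slope rk of follow-up on baseline approaches 1. With k = 1.2, r = 0.5 and 10% missing, simulation gave 6.6%. The combination of k = 0.8 with drop-out was not simulated.

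**Step 5: comparators and precision.** On the same simulated data, ANCOVA of week-10 pain rejected in 4.8% to 5.4% of trials, and the mixed model without the baseline covariate in 4.7% to 5.6%. With complete data the covariate takes the same value in both of a worker's records and cancels from group-by-time. At r = 0.5 the true SD of the estimate is 0.250 with or without it, against 0.225 for ANCOVA. In theory ANCOVA has (1−r²)/[2(1−r)] = (1+r)/2 of the change-score variance: 0.65, 0.75 and 0.85 at r = 0.3, 0.5 and 0.7, before the small cost of adjusting for the imbalanced age.

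**The case against.** The strongest reply is that the inflation depends on a fitting choice that the article does not state. It names neither REML nor a zero bound. In a classical repeated-measures ANOVA, group-by-time is tested against the within-subject mean square, which a between-subject covariate leaves unchanged when data are complete. A compound-symmetric fit that allows negative covariance does the same. In simulation (33 per arm, 1,500 trials per setting, equal SDs) such a fit rejected in 4.3% to 5.7% of trials. This stands, and it makes the conclusion conditional. It does not clear the plan: a subject random effect in a mixed model is most naturally fitted with a non-negative variance, and with 10% drop-out the unbounded fit still rejected in 5.6% to 6.7%.

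It is also fair that r and k are unknown, that the excess is modest, and that a journal article leaves software settings to the full plan. But the conflicting ingredients are all stated in the article, so this is not a matter of omitted detail.

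Three stronger readings are tempting, and the document supports none of them.
- That the model always forces the subject variance to zero. The negative value is an expectation. The estimate was at the bound in 90% to 100% of simulated trials with equal SDs and complete data (r up to 0.8), and in 65% to 100% over a wider set of settings.
- That the type I error is near 15%. That figure (SE ratio 0.73 at r = 0.5) would apply if the week-10 least-squares mean difference from this model were reported. The article describes the difference from baseline to follow-up, which is the group-by-time contrast.
- That the effect estimate is biased or the trial underpowered. With complete data the estimate is the raw difference in change, and the sample size was planned for 95% power.

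**Conclusion.** The point holds in conditional form. The double use of baseline pain follows directly from the stated model and the two measurement times. If the subject effect is fitted as a variance bounded at zero, the group-by-time standard error is usually too small: by about 9%, 6% and 4% at r = 0.3, 0.5 and 0.7 with equal SDs and complete data. The type I error is then about 5% to 9% instead of 5%, depending on a correlation and an SD ratio that the protocol does not give. It is roughly 5.5% to 7.5% for equal SDs, r of 0.3 to 0.7 and complete data, and generally higher at the protocol's own 10% drop-out. It is near nominal with complete data if the covariance may go negative. In the complete-data case the baseline covariate adds no precision to the reported contrast. The excess is modest, but it affects the only model given for the primary outcome, and DASH through it.

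**What to change.** Replace the model sentence with an ANCOVA: 10-week average pain (or its change from baseline) as the single response, group as the factor, and baseline average pain, gender, workplace and age as covariates. Report the adjusted group difference with its 95% confidence interval.

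If a repeated-measures model is preferred, so that workers without follow-up stay in the analysis, use a longitudinal model with baseline as a response only: common baseline mean in the two groups, unstructured 2×2 covariance, and no baseline covariate. Gender, workplace and age can remain.

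Make the same change for the DASH work module. The cost is one sentence of analysis wording and a simple SAS call, with no new data and no change to the sample size. It should be settled before the unblinded analysis.

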### Randomization

On the basis of the clinical examination and associated questionnaire we randomly allocated the 66 eligible participants, using a computer-generated random numbers table (SAS), to either strength training intervention or ergonomic counseling. Gender and worksite (2 slaughterhouses) were used as stratification variables. Subsequently, participants were informed by letter about group allocation. At the follow-up physical examination and questionnaire in Dec 2012-Jan 2013, all examiners were blinded, and participants instructed not to reveal their particular intervention. Baseline characteristics and pain score of employees randomized into the two intervention groups are illustrated in Table 2.

**Table 2 T2:** Characteristics of the two intervention groups

	**Participatory ergonomics**	**Strength training**
N	33	33
Number of men/women	26/7	25/8
Age (years)	43 (9)	48* (9)
Height (cm)	177 (9)	174 (10)
Weight (kg)	86 (17)	83 (20)
BMI (kg∙m^-2^)	28 (5)	28 (6)
Shoulder pain intensity during the last week (scale 0–10)	5.7 (2.0)	5.6 (2.2)
Elbow/Forearm pain intensity during the last week (scale 0–10)	4.2 (2.4)	4.1 (2.9)
Hand/Wrist pain intensity during the last week (scale 0–10)	3.7 (2.6)	3.9 (2.8)

Values are means (SD) * denotes significant difference between groups, P < 0.05.

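### As listed, the repeated-measures model does not carry its stated adjustment for age, gender, workplace and baseline pain into the reported baseline-to-follow-up contrast

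*Protocol article*

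**What the plan says.** The Statistical analysis section names a "repeated-measures two-way analysis of variance (ANOVA) with *group*, *time* and *group by time* as independent variables". It adds "Subject is entered as a random effect" and "Analyses are adjusted for gender, workplace, age and pain intensity at baseline". The result to be published is described thus: "Outcomes will be reported as between-group least square mean differences and 95% confidence intervals from baseline to follow-up". Missing values are to be handled "using a Mixed model approach which inherently accounts for missing values".

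Outcome measures fixes the number of time points at two: "at baseline and after the 10 week intervention period". Primary outcome measures defines the endpoint: "The primary outcome is the change from baseline to 10-week follow-up in pain intensity during the last week". Secondary outcome measures applies the same analysis to the DASH work module.

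Under Randomization, gender and worksite are the stratification variables and age is not. Table 2 gives age as 43 (9) years with ergonomics and 48 (9) with strength training, 33 workers per arm. It marks this row alone as different, with the footnote "Values are means (SD) * denotes significant difference between groups, P < 0.05".

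**The concern.** With two time points, a model that has a time factor must hold baseline pain as one of its two responses. The between-group difference from baseline to follow-up is then the group-by-time contrast. Age, gender, workplace and baseline pain each take one value per worker. If they enter without a time interaction, and none is listed, they move both of a worker's records by the same amount and say nothing about the change.

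The publication would then describe its main estimate as adjusted for age and the stratification factors when the adjustment has not acted on it. For age this matters in practice: the arms differ by 5 years, the design did not balance age, and the model is the only place left to deal with it.

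**Working it through.** **Inputs.** Table 2: age 43 (9) v 48 (9), n = 33 per arm; regional pain means. Sample size section: SD 1.5, relevant difference 1.5, 27 per group for 95% power, 10% dropout. Statistical analysis section: model terms. The slope of change in pain on age is not in the article and is assumed.

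**1. The article's own figures.** Age: standard error = 9 × √(2/33) = 2.216; t = 5/2.216 = 2.26 on 64 df; two-sided p = 0.027. This agrees with the flag. The means are rounded to whole years, so the true gap could lie between about 4 and 6 years. Sample size: 27 per group with difference 1.5 and SD 1.5 gives 95.0% power (two-sided t test), and 27/0.9 = 30. The 1.5 points is therefore a usable yardstick.

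**2. The contrast.** Write pain of worker i at time t (0 or 1) as

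y_it = μ + α·g_i + τ·t + δ·g_i·t + β′x_i + u_i + e_it,

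with x_i the four covariates and u_i the subject effect. Subtracting,

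y_i1 − y_i0 = τ + δ·g_i + (e_i1 − e_i0).

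Both β′x_i and u_i have gone. With complete data the estimate of δ is D, the raw difference in mean change. Fitted random-intercept models with 33 + 33 simulated workers confirm this: the group-by-time estimate agreed to 8 decimals with no covariates, with age, gender and workplace, and with baseline pain added.

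**3. If the follow-up difference from the same model is reported instead.** The worker's mean (y_i0 + y_i1)/2 is regressed on group and covariates, baseline pain included. The y_i0 half is fitted perfectly by itself and contributes no group effect. The y_i1 half contributes A/2, where A is the ANCOVA estimate. Adding half the interaction, the follow-up difference is A/2 + D/2. The adjustment acts by half.

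**4. With dropout.** At 10% random dropout the simulated group-by-time estimate moved by at most about 0.04 points with age, gender and workplace in the model, and about 0.10 with baseline pain added. These movements averaged about zero. For an assumed slope of +0.05 points per year (25 runs), mean estimates were -0.565 without covariates, -0.564 with main effects and -0.858 with covariate-by-time terms. Only the last takes out the age shift.

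**5. Size of the age shift.** Shift = 5 years × slope of *change* in pain on age.

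| Assumed slope (points/year) | Shift | Share of 1.5 |
|---|---|---|
| -0.06 | -0.30 | 20% |
| -0.02 | -0.10 | 7% |
| 0 | 0 | 0% |
| +0.02 | +0.10 | 7% |
| +0.06 | +0.30 | 20% |

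A check by simulation (complete data, true effect -1.0, 4,000 runs per slope) gave mean contrasts of -0.752 at +0.05 and -1.248 at -0.05. With an age-by-time term both were -0.999.

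**6. Baseline pain.** The three regional means average 13.6/3 = 4.53 in each arm (5.7 + 4.2 + 3.7 and 5.6 + 4.1 + 3.9). An inert baseline covariate therefore hardly shifts this estimate, but it costs precision. With equal SDs at both times and correlation r, the ANCOVA variance is (1 − r²)/(2(1 − r)) = (1 + r)/2 of the change-score variance, or 0.75 at an assumed r of 0.5.

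**The case against.** The article does not say in so many words that the covariates are main effects only. That is inferred from the listed terms, and a condensed article may leave exact terms to a fuller plan. This stands, and it is why the point is tied to the natural reading. It is still more than a missing detail: the listed model, the stated adjustment and the reported contrast do not work together if followed as written.

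A second defence is that the endpoint is a change score with baseline pain as covariate, which resembles an ANCOVA, and there the adjustment would act. But a single response per worker leaves no time factor, and the section names one. Within the named model even the follow-up difference is only half adjusted (step 3).

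A reader might infer more than the article supports:

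- *That the covariates cannot change the estimate at all.* This is exact only with complete data; with the planned-for dropout the estimate moves a little.
- *That the age gap biases the result.* An age effect shared by baseline and follow-up cancels. Only a slope of change on age matters, and the article shows none. It could be zero or of either sign.
- *That the trial's false-positive rate is inflated.* The gap arose by chance under randomisation. With age gaps left random, the change-score test rejected in 5.5% of simulated null trials, about nominal. Fixing the gap at 5 years and assuming a slope of 0.04 raises this to about 7%, but that describes the assumed setting only. Using baseline pain as both response and covariate raises rejection further even at slope zero (6.6% against 4.6%), which is a separate fault.

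**Conclusion.** The point holds on the natural reading of the Statistical analysis section. With complete data the stated adjustment for age, gender, workplace and baseline pain leaves the reported contrast equal to the unadjusted difference in mean change. With about 10% dropout it alters the contrast slightly and leaves the age shift in place.

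The consequence is a possible shift in the estimate, given the observed 5-year imbalance, of -0.30 to +0.30 points for assumed slopes of -0.06 to +0.06 points per year. That is at most 20% of the 1.5-point relevant difference. Any precision the covariates could buy is also forgone. The effect would be reported as adjusted when it is not. The size rests wholly on the assumed slope and on the rounded gap in Table 2. The change should be made, but the article gives no ground for calling the trial's conclusion invalid.

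**What to change.** State the response and the contrast, and choose one of two models:

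1. Preferred: an ANCOVA of 10-week pain (or of change) on group, with baseline pain, age, gender and workplace as covariates. There is no time factor, and the group coefficient is the reported effect.
2. If the repeated-measures model is kept: remove baseline pain from the covariates, since it is already a response, and add age-by-time, gender-by-time and workplace-by-time terms. The group-by-time contrast is then adjusted for all three.

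Apply the same choice to the DASH work module. The covariates are those already named, so nothing is selected after the fact. The section describes the analysis in the future tense, so the wording can be settled while the analysts are still blinded.

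The cost is three degrees of freedom for the interaction terms, or four for the ANCOVA covariates, out of 64. Adjusting for an unbalanced age also has a small price: the squared group–age correlation is 2.26²/(2.26² + 64) = 0.074, so the variance rises by a factor of 1/(1 − 0.074) = 1.08 before any gain from the covariates.
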